### **5.4 DEVIATIONS AND SERIOUS BREACHES**

Any study protocol deviations/violations and breaches of Good Clinical Practice occurring at sites should be reported to the SCTU and the local R&D Office immediately. SCTU will then advise of and/or undertake any corrective and preventative actions as required.

All serious protocol deviations/violations and serious breaches of Good Clinical Practice and /or the study protocol will immediately be reported to the regulatory authorities and other organisations, as required in the Medicines for Human Use (Clinical Trials) Regulations 2004, as amended.

### **5.5 STUDY DISCONTINUATION**

In consenting to the study, participants have consented to the study intervention and data collection. Participants may be discontinued from the study procedures at any time.

#### **5.5.1 *Reasons for study discontinuation***

Participants may be discontinued from the study in the event of:

- Clinical decision, as judged by the Principal Investigator or Chief Investigator
- In the event the trial is discontinued due to the interim analysis (as outlined in Section 7.3)

Full details of the reason for study discontinuation should be recorded in the eCRF and medical record.

### **5.6 WITHDRAWAL**

The participant / legal representative is free to withdraw consent from the study at any time without providing a reason.

Investigators should explain to patients the value of remaining in study follow-up and allowing this data to be used for trial purposes. Where possible, patients who have

withdrawn from study treatment should remain in follow-up as per the trial schedule. If patients additionally withdraw consent for this, they should revert to standard clinical care as deemed by the responsible clinician. It would remain useful for the study team to continue to collect standard follow-up data and unless the patient explicitly states otherwise, follow-up data will continue to be collected.

Details of study discontinuation (date, reason if known) should be recorded in the CRF and medical record.

## 5.7 PROHIBITED AND RESTRICTED THERAPIES DURING THE STUDY

There are no prohibited or restricted therapies during this study.

## 5.8 BLINDING AND PROCEDURES FOR EMERGENCY UNBLINDING

Due to the nature of the interventions in this trial there will be no blinding of participants or investigators.

# 6 SAFETY

## 6.1 DEFINITIONS

**Adverse Event (AE):** any untoward medical occurrence in a participant or clinical study participant which does not necessarily have a causal relationship with study treatment or participation.

An AE can therefore be any unfavourable and unintended sign (including an abnormal laboratory finding), symptom, or disease temporally associated with the study treatment or participation (regardless of causality assessments).

**Serious Adverse Event (SAE)** is any untoward medical occurrence or effect that:

- **Results in death**
- **Is life-threatening** – *refers to an event in which the participant was at risk of death at the time of the event; it does not refer to an event which hypothetically might have caused death if it were more severe*
- **Requires hospitalisation, or prolongation of existing hospitalisation**
- **Results in persistent or significant disability or incapacity**
- **Is a congenital anomaly or birth defect**
- Other important medical events\*\*\*.

\*‘life-threatening’ in the definition of ‘serious’ refers to an event in which the patient was at risk of death at the time of the event; it does not refer to an event which hypothetically might have caused death if it were more severe.

\*\*Hospitalisation is defined as an inpatient admission, regardless of length of stay, even if the hospitalisation is a precautionary measure for continued observation. Hospitalisations for a pre-existing condition, including elective procedures that have not worsened, do not constitute an SAE.

\*\*\*Other important medical events may also be considered serious if they jeopardise the participant or require an intervention to prevent one of the above consequences.

**Note:** It is the responsibility of the PI or delegate to grade an event as ‘not serious’ (AE) or ‘serious’ (SAE).

## 6.2 SERIOUSNESS

A complete assessment of the seriousness must always be assessed by a medically qualified doctor who is registered on the delegation of responsibility log; this is usually the investigator.

All adverse events that fulfil the criteria definition of 'serious' in protocol section 6.1, must be reported to SCTU using the Serious Adverse Event Report Form – Non-CTIMP. Specific exceptions to this (as listed below) should be recorded as AEs rather than SAEs.

All SAEs must be reported immediately by the PI at the participating centre to the SCTU.

### 6.2.1 Exceptions:

For the purposes of this study, the following SAEs **do not** require reporting to SCTU using the Serious Adverse Event Report Form – Non-CTIMP:

- Hospitalisations for elective treatment of a pre-existing condition

## 6.3 CAUSALITY

A complete assessment of the causality must always be assessed by a medically qualified doctor who is registered on the delegation of responsibility log; this is usually the investigator.

If any doubt about the causality exists the local investigator should inform the SCTU who will notify the Chief Investigator. Other clinicians may be asked for advice in these cases.

| Relationship      | Description                                                                                                                                                                                                                                                                                                        | Event Status                                            |
|-------------------|--------------------------------------------------------------------------------------------------------------------------------------------------------------------------------------------------------------------------------------------------------------------------------------------------------------------|---------------------------------------------------------|
| Unrelated  | There is no evidence of any causal relationship                                                                                                                                                                                                                                                                    | Not related to treatment                                |
| Unlikely   | There is little evidence to suggest there is a causal relationship (e.g. the event did not occur within a reasonable time after administration of the study treatment). There is another reasonable explanation for the event (e.g. the participant's clinical condition, other concomitant treatment).            | Not related to treatment                                |
| Possibly   | There is some evidence to suggest a causal relationship (e.g. because the event occurs within a reasonable time after administration of the study treatment). However, the influence of other factors may have contributed to the event (e.g. the participant's clinical condition, other concomitant treatments). | Related and expected SAE/
Related and unexpected SAE |
| Probably   | There is evidence to suggest a causal relationship and the influence of other factors is unlikely.                                                                                                                                                                                                                 | Related and expected SAE/
Related and unexpected SAE |
| Definitely | There is clear evidence to suggest a causal relationship and other possible contributing factors can be ruled out.                                                                                                                                                                                                 | Related and expected SAE/
Related and unexpected SAE |

In terms of event status; **Not related to treatment** would highlight that the SAE is not related to the trial treatment. **Related and expected** SAE would signify that the SAE is

related to the trial treatment and is expected (according to the list of expected events listed in the protocol). **Related and unexpected SAE** would be classified as an SAE which is related to the trial treatment and is unexpected in terms of the events listed in the protocol.

In the case of discrepant views on causality between the Investigator and others, SCTU will classify the event as per the worst case classification I and where applicable the Ethics Committee will be informed of both opinions within the required timelines.

## 6.4 EXPECTEDNESS

Expectedness assessments are made against the list of expected events below:

### 6.4.1 *Expected Adverse Events:*

- Minor musculoskeletal aches and pains
- Myocardial infarction
- Known adverse effects of medications used in the intervention as per the SPCs.

The nature or severity of should be considered when making the assessment of expectedness. If these factors are not consistent with the current information available then the AE should be recorded as 'unexpected'.

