#### **5.2 STUDY PROCEDURES**

Patients will have an initial consultation with an OCTOPuS trained health professional (OCTOPuS Practitioner), who may be a nurse, pharmacist, or other appropriately trained person. In this consultation the patient's diabetes management will be discussed, as well as the likely benefits that improved glycaemic control will provide in the run up to surgery. The practitioner and patient will agree a number of actions, tailored to the individual needs and ability. These are likely to include:

- A graded exercise regimen. This may be completely self-delivered, or alternatively by joining a local appropriate exercise scheme – such as a 'health walk'. There is a general consensus among the cardiothoracic community that limited exercise can be

allowed prior to surgery. This needs to be individualised for each patient, and should not provoke symptoms of angina or breathlessness. The usual format of exercise suggested is walking on the flat, for short, frequent, episodes.

- Dietary advice, possibly supplemented by a consultation with a dietitian
- Medication review, which may lead to the introduction of insulin for people with type 2 diabetes.
- Specific advice about managing expectations, understanding facilitators to achieve change and overcoming barriers to improve medical and psychosocial outcomes

Patients will receive regular review with the OCTOPuS practitioner, probably by telephone, at least once a fortnight. This will be an opportunity to offer encouragement and support, and address any issues which have arisen for the patient.

Where necessary the OCTOPuS practitioner will liaise with local services, e.g. the patient's GP or a dietitian, to facilitate delivery.

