### **6.6 SCTU RESPONSIBILITIES FOR SAFETY REPORTING TO REC**

SCTU will notify the necessary competent authorities of all **Related and Unexpected** SAEs occurring during the study within 15 days.

SCTU submit all safety information to the REC in annual progress report.

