## **7 STATISTICS AND DATA ANALYSES**

### **7.1 SAMPLE SIZE**

It is expected that the intervention development will require approximately 20 participants. This number is based on cycles of 4-6 patients with up to 4 iterative cycles. This figure is based on previous experience of the Chief Investigator from a similar trial where a more complex intervention was developed (14).

Feasibility data analysis will be descriptive: recruitment rates, participant characteristics, acceptability of trial procedures and process variables.

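### Listing myocardial infarction as expected, without limits, means a related infarction by default skips the 15-day notification and reaches the REC only in the annual report

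*Protocol*

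**What the plan says.** Section 6.4.1 gives three kinds of expected event: minor musculoskeletal complaints, "Myocardial infarction", and "Known adverse effects of medications used in the intervention as per the SPCs". The infarction entry stands alone, without grade, outcome, timing or setting. A proviso follows: nature or severity "should be considered when making the assessment of expectedness", and "If these factors are not consistent with the current information available then the AE should be recorded as" unexpected.

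Section 6.3 sets the event status. SAEs judged unrelated or unlikely are not related to treatment. Those judged possibly, probably or definitely related are split by expectedness. An SAE is *related and expected* if it is "related to the trial treatment and is expected (according to the list of expected events listed in the protocol"). *Related and unexpected* is likewise defined by the listed events, without mention of the proviso. Section 6.5.5 tells the investigator to assign expectedness by reference to 6.4.1.

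Reporting has two stages. Sites send every SAE to SCTU immediately (6.2) or within 24 hours (6.5.1, 6.5.5); the only exception is elective hospitalisation for a pre-existing condition (6.2.1). From SCTU outward, Section 6.6 requires notification of related and unexpected "SAEs occurring during the study within 15 days". All safety information goes to the REC in the annual progress report.

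**The concern.** Expectedness changes the reporting path only for SAEs judged at least possibly related. An unqualified infarction entry therefore takes infarctions that have been linked to the intervention off the 15-day path. The intervention includes a graded exercise regimen for people awaiting cardiac surgery (Section 5.2), so an infarction that an investigator links to it is an event that an outside body would want to hear of promptly.

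Timing makes this matter more. Under Section 2 the intervention is tested in groups of 4-6 people and refined over 3-4 cycles within a nine-month development period. A signal that reaches the REC on a yearly schedule may arrive when there is no cycle left to change.

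**Working it through.** There is no statistical figure to reproduce: the protocol says "Feasibility data analysis will be descriptive", and it gives no infarction rate. The check is to follow one event through Section 6 and then compare the timings.

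**Path of an infarction judged possibly related**

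1. *Site to SCTU (6.2, 6.2.1, 6.5.1, 6.5.5).* It is an SAE and not the elective-hospitalisation exception, so it reaches SCTU within 24 hours. Expectedness plays no part here.
2. *Causality (6.3).* The possibly, probably and definitely rows all lead to a related status.
3. *Expectedness (6.3, 6.4.1, 6.5.5).* Infarction is on the list, so the default is *related and expected*.
4. *Proviso (6.4.1).* It could move the event to unexpected if nature or severity is inconsistent with current information. As the text reads, the words after "of" that should say whose nature or severity is meant are missing. Supplying the obvious noun does not settle the matter, because no severity or reference document is given for infarction. The drug entry, by contrast, points to the SPCs. Section 6.3 does not carry the proviso at all. An assessor could in good faith class a fatal related infarction as expected.
5. *SCTU outward (6.6).* As *related and expected*, it is outside the 15-day requirement. The next route to the REC that the protocol requires is the annual report.

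The entry also has no time limit. Section 6.5.2 applies event reporting up to 30 days after surgery, so the same two words cover an infarction during the exercise programme and one after the operation.

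**Timing**

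If the infarction occurs *t* months after the last annual report (or after the start of the reporting year), the wait for the next one is 12 − *t* months:

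- *t* = 0: 12 months
- *t* = 6: 6 months
- *t* = 11.5: 0.5 month, about the same as 15 days

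The annual route is therefore slower for nearly the whole year.

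The protocol does not say when the reporting year starts. Assume it starts *k* months before the first cycle, so that the first report falls at month 12 − *k* of the nine-month period:

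- *k* = 0: month 12, which is 12 − 9 = 3 months after the period ends
- *k* = 3: month 9, as the period ends
- *k* = 6: month 6, within the period; an infarction in months 6 to 9 would then wait until month 18

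So the annual report may come after the cycles have ended. Whether it does depends on *k* and on when the event occurs.

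**The case against.** The strongest reply is that nothing is hidden from the people running the study. Every SAE is with SCTU within a day. Where causality is in doubt, SCTU notifies the Chief Investigator (6.3), who chairs the TMG (11.1). The TSC, most of whose members should be independent, reviews a report before recommending whether to proceed to the main trial (2.1.5, 11.2). This stands. A reader might infer that related infarctions escape all expedited reporting, or are seen by nobody until the annual report. The protocol does not support either reading; only the step out of SCTU is delayed.

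Second, listing infarction has a rationale. It is foreseeable in people awaiting cardiac surgery, and the possibly row of Section 6.3 allows for a contribution from the participant's own condition while still counting the event as related. Discrepant views on causality go to the worst case. So the entry does not act only on infarctions that the intervention truly caused; it also spares notification of some background events. This stands too. It is a cost of the fix, but not a reason to hold back the related events as a class.

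Third, a reader might see a contradiction with Section 5.2, which says of exercise: "This needs to be individualised for each patient, and should not provoke symptoms of angina or breathlessness". That is guidance on how exercise is set. A list of expected events may recognise a risk that remains despite such precautions, so the two can coexist.

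Fourth, the drug-effects entry might seem open to the same criticism. It is not, because it names the SPCs as the reference against which nature and severity can be judged. Expediting every serious known drug effect would be a preference, not the correction of an error.

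Finally, the proviso does let an assessor record an infarction as unexpected. That is why the classification is a default and not a certainty. Its wording gives the assessor little to work with.

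**Conclusion.** The point holds in a limited form. By default, an infarction judged related to the intervention, whatever its severity or outcome, is *related and expected*. It reaches SCTU within 24 hours, is not notified onward within 15 days, and reaches the REC in the annual report, which can mean a wait of up to 12 months. The proviso in 6.4.1 is too incomplete to be relied on to change this.

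This rests on reading 6.3, 6.4.1 and 6.6 as written and on assessors following the list unless they have a stated reason not to. It needs no assumption about how often infarction occurs. The size cannot be put as a number of events, since the protocol gives no rate.

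This is a worthwhile, cheap improvement to safety oversight and not a defect that must be cured before the study can proceed. No SAE goes unreported to SCTU, and no endpoint or analysis changes.

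**What to change.** Make three linked edits, all to reporting classification:

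1. Delete the infarction entry from 6.4.1. Alternatively, keep it and state in both 6.4.1 and 6.6 that any infarction judged possibly, probably or definitely related is notified within 15 days.
2. Complete the proviso sentence in 6.4.1, so that it says whose nature or severity is assessed and against what information.
3. Align the definition of unexpected in 6.3 with that proviso, so that the two sections give the same answer for the same event.

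The drug-effects entry can stay as it is.

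The cost is a short protocol amendment and one extra notification for each infarction judged related. With about 20 participants (Section 7.1) that should be at most a few, some of them background infarctions judged possibly related. Infarctions judged unrelated or unlikely are unaffected.

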## 6.5 REPORTING PROCEDURES

All adverse events should be reported.

Depending on the nature of the event, the appropriate reporting procedures below should be followed. A flowchart will be provided to aid in the reporting procedures.

### 6.5.1 *Reporting Details*

A SAE for Non-CTIMPs Form should be completed for all SAEs and faxed to SCTU within 24 hours of site becoming aware of the event.

Complete the SAE form and fax or email a scanned copy of the form with as many details as possible to the SCTU together with anonymised relevant treatment forms and investigation reports.

**Or**

Contact the SCTU by phone for advice and then fax or email a scanned copy of the completed SAE form.

#### **6.5.2 Follow Up and Post- study SAEs**

The reporting requirement for all AEs and SAEs affecting participants applies for all events occurring up to 30 days following cardiac surgery.

All unresolved adverse events should be followed by the investigator until resolved, the participant is lost to follow-up, or the adverse event is otherwise explained. At the last scheduled visit, the investigator should instruct each participant to report any subsequent event(s) that the participant, or the participant's general practitioner, believes might reasonably be related to participation in this study. The investigator should notify the study sponsor of any death or adverse event occurring at any time after a participant has discontinued or terminated study participation that may reasonably be related to this study.

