| Physical Exam (incl height, weight and waist circumference)                                                       |               | X                    |                     |                     |                     |                     |                      |                                   | X       |           |
| Vital Signs (incl. BP)                                                                                            |               | X                    |                     |                     |                     |                     |                      |                                   | X       |           |
| Biochemistry (incl HbA 1c , blood glucose and renal function)                                          |               | X                    |                     |                     |                     |                     |                      |                                   | X       |           |
| Intervention                                                                                                      |               | X                    |                     |                     |                     |                     |                      |                                   |         |           |
| Intervention support phone call a (incl. review of diary card and components of intervention utilised) |               |                      | X                   | X                   | X                   | X                   | X                    | X                                 |         |           |
| Surgery                                                                                                           |               |                      |                     |                     |                     |                     |                      |                                   | X       |           |
| Adverse Events                                                                                                    |               | X                    | X                   | X                   | X                   | X                   | X                    | X                                 | X       | X         |

|                       |  |   |  |  |  |  |  |  |  |                |
|-----------------------|--|---|--|--|--|--|--|--|--|----------------|
| Qualitative Interview |  | X |  |  |  |  |  |  |  | X b |

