| Time to discharge     |  |   |  |  |  |  |  |  |  | X              |
| Surgery details       |  |   |  |  |  |  |  |  |  | X              |

a further support calls may be needed at fortnightly intervals if the surgery is delayed beyond 12 weeks from listing. These phone consultations will not produce data to be captured, but will prompt phone discussion regarding adherence to the intervention and/or during interviews.

b interviews will be conducted within 6 weeks of surgery.

**NB:** The Participant/legal representative is free to withdraw consent at any time without providing a reason. When withdrawn, the participant will continue to receive standard clinical care. Follow up data will continue to be collected unless the participant/legal representative has specifically stated that they do not want this to happen.

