### 4.2 INCLUSION CRITERIA

- Adults (aged 18-75 yrs) with sub-optimally controlled type 1 or type 2 diabetes. Sub-optimal control is defined as an  $HbA_{1c} > 53$  mmol/mol using a near patient test at the cardiothoracic outpatients appointment where the decision to proceed to surgery is made.
- Awaiting elective cardiac surgery, where it is anticipated the delay before surgery will be at least 3 months.
- Ability to give informed consent.
- Ability to interact with the study documentation and processes.

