### **5.3 FOLLOW UP**

Patients will be interviewed within 6 weeks of receiving their surgery.  
Follow up will be as per local practice.

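### Adverse events must be reported to day 30 after surgery, but the schedule stops collecting them at discharge and no later study contact is given the task

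*Protocol*

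**What the plan says.** Section 6.5.2 sets the safety window: "The reporting requirement for all AEs and SAEs affecting participants applies for all events occurring up to 30 days following cardiac surgery". Section 6.5 is equally broad: "All adverse events should be reported".

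In the schedule of observations, the row "Adverse Events" is marked at Screening & Baseline, at each support call from week 2 to week 12, at Surgery and at Discharge. Discharge is the last column, and the adverse event mark there carries no footnote.

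On what follows discharge, section 5.3 says: "Patients will be interviewed within 6 weeks of receiving their surgery" and "Follow up will be as per local practice". The schedule shows this interview in the Discharge column with its own footnote (b), which gives the 6-week limit.

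Section 6.5.2 also provides that, at the last scheduled visit, participants are told to report later events that they or their general practitioner "believes might reasonably be related to participation in this study". Section 3.3 ties the end of the study to the last participant's last interview.

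On the support calls needed when surgery is delayed past week 12, footnote a says: "These phone consultations will not produce data to be captured".

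**The concern.** The safety section asks for every event to day 30, while the schedule gives nobody the task of asking after discharge. A site could complete every scheduled item and still not have the information that section 6.5.2 requires.

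The events most exposed are ones that the protocol itself treats as important. Section 1.1 names wound and chest infection, renal impairment and death as risks of poor glycaemic control around cardiac surgery, and says that people with diabetes have higher re-admission rates. Under section 6.1, an unplanned admission for a new event is a serious adverse event, and a re-admission necessarily comes after discharge. A low post-discharge count from this pilot could mean few events, or only that no one asked.

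**Working it through.** The protocol gives no event rate or safety figure to reproduce, so the check compares the required window with the scheduled contacts.

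**1. Required window.** All adverse events and serious adverse events, from consent (6.5.4) to day 30 after surgery (6.5.2).

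**2. Scheduled collection.** From baseline to Discharge (schedule). No day-30 contact is listed.

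**3. Contacts after discharge.** One interview, at any time up to 6 weeks = 42 days after surgery (5.3 and footnote b). Section 7.2 describes its content as perceptions, experiences and possible improvements; adverse events are not mentioned. An interview on day 20, say, would comply and would leave days 21 to 30 with no later study contact.

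**4. Fallback.** If Discharge is the last scheduled visit, what remains is self-report limited to events believed related to the study. That is narrower than the all-events duty, and it would start while the 30-day window is still open. The protocol does not say which contact is the last scheduled visit, so this step is conditional.

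**5. Length of the gap.** Days without scheduled collection = 30 − length of stay. The cardiac stay is not given, so the stays below are assumptions.

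| Assumed stay (days) | Gap (days) | Share of 30 days | Participant-days, n = 20 (of 20 × 30 = 600) |
|---|---|---|---|
| 7 | 30 − 7 = 23 | 77% | 20 × 23 = 460 |
| 10 | 30 − 10 = 20 | 67% | 20 × 20 = 400 |
| 14 | 30 − 14 = 16 | 53% | 20 × 16 = 320 |

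The only stays in the protocol are the Bournemouth means of 5.9 and 3 days (1.1). They would give gaps of 24.1 and 27 days, but they are not stated to be for cardiac surgery and are not relied on here.

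**6. Room for a remedy.** An interview on or after day 30 and within the existing 6-week limit has a slot of 42 − 30 = 12 days.

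**The case against.** The strongest reply is that a reporting window and a visit grid are different things. Serious events are reported when the site becomes aware of them (6.5.1, 6.5.5), hospital records are source data (13.3), and there is one centre. So the window may be longer than the schedule without a strict contradiction, and many post-discharge events would reach the site anyway. This is fair as far as it goes: a site could meet 6.5.2 by its own efforts. But the awareness trigger fixes when to report, not how events are found, and section 4.1 accepts that the hospital may be far from the patient's home, so its own records may not show an admission elsewhere.

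A second reply is that the Discharge column also holds the interview and so extends to 6 weeks. However, the interview has a footnote that says so and the adverse event mark does not. Even on the generous reading, the interview may fall before day 30.

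Third, section 3.3 adds that all data needed for the research question must have been captured. That softens the end-of-study point, but the research question is acceptability, so the clause does not clearly secure 30-day safety data.

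A reader might also infer that collection fails before surgery too, because footnote a excludes data from calls after week 12 and eligibility specifies "Awaiting elective cardiac surgery, where it is anticipated the delay before surgery will be at least 3 months". The documents do not support this. Adverse events are marked at Surgery, section 6.5.4 requires any event after consent to be recorded, and the footnote sits on the intervention support-call row and goes on to discuss adherence. The effect is at most a longer recall period, with a scheduled collection at its end.

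**Conclusion.** The mismatch after discharge is real: an all-events duty to day 30 has no scheduled means of collection once the participant leaves hospital. With an assumed stay of 7 to 14 days, 23 to 16 of the 30 days are uncovered. That range rests on the assumed stay and on reading the adverse event mark at Discharge as made at discharge. The mismatch itself does not depend on the figure chosen. How many events would be missed cannot be estimated, because the protocol gives neither a post-discharge event rate nor a rate of self-report.

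A reader might go further and infer that the Trial Steering Committee will decide whether to proceed on an incomplete adverse event count. Section 2.1.5 does not say that. The progression rule turns on whether an acceptable manual and training package can be produced, and it names no adverse event count. The point is therefore about the quality of the pilot's safety record. It is worth correcting because the correction is cheap, and it does not undermine the acceptability aim.

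**What to change.** 1. **Schedule:** add an adverse event and serious adverse event check at days 30 to 42 after surgery. Make it at the planned interview, or by a brief telephone call or notes review where the interview is held earlier or declined.
2. **Section 6.5.2:** state that the last-scheduled-visit instruction is given at this contact and covers events after it.
3. **Section 3.3:** make the end of study no earlier than the last such contact.
4. **Footnote a (clarification only):** say that adverse events disclosed at calls after week 12 are recorded on the AE CRF.

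**Cost.** If the check is paired with the interview, the slot narrows to the 12 days from day 30 to day 42. If a separate call is used, at an assumed 15 minutes each it takes 20 × 15 / 60 = 5 hours of staff time for 20 participants, or 30 × 15 / 60 = 7.5 hours for 30. The other changes are wording. Recruitment and the intervention are unaffected.
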